#### Blinding

Following the allocation to one of the interventions, the outcome assessors will be blinded to the participants’ group assignment. Due to the nature of the intervention in the experimental group (VRSCT), participants, therapists conducting the intervention, and the clinicians managing TAU will not be blinded to the received interventions. Participants will be instructed prior to follow-up assessments not to disclose their allocation to the outcome assessors. To maintain blinding, assessments and interventions will be conducted at separate locations, ensuring that the assessors remain unaware of group assignment. Assessors will be instructed to notify their supervisors immediately if they believe blinding has been broken. If unblinding of the outcome assessor occurs, another outcome assessor blind to the allocation of intervention will conduct the subsequent assessments.

### Data Collection

#### Assessment and Collection of Outcomes

Assessments will be conducted at baseline (t_0_), 3 months post baseline (t_1_), and 6 months post baseline (t_2_). An overview of assessments and outcome measures is provided in Table 1. Outcome assessors will be psychologists who will receive comprehensive training before conducting assessments. To ensure consistency and maintain data quality, assessors will participate in monthly supervision sessions focused on the administration and scoring of assessments. The following rater-based assessments, HiSoC, PSP, and SSPA, will be video- and audio-recorded to enable subsequent scoring. To ensure high interrater reliability, a structured calibration procedure has been implemented. First, the initial 20 consecutive assessments of each rater-based measure will be scored through consensus by the 2 outcome assessors together with a senior researcher and clinical expert in autism. This process is used to establish a shared understanding of scoring criteria and interpretation. Subsequently, the next 10 consecutive assessments will be independently rated by both outcome assessors, and intraclass correlation coefficients will be calculated to evaluate interrater agreement. Provided that acceptable reliability is achieved (intraclass correlation coefficient ≥0.75) [84], the assessors will continue to rate independently. To prevent rater drift and ensure continued data quality throughout the trial, monthly consensus rating sessions will be conducted involving both assessors and the senior researcher. Further, the assessment of co-occurring psychopathology using the MINI will be scored through consensus. Diagnoses based on the MINI will be diagnosed according to both *ICD-10* and *ICD-11* (*International Classification of Diseases, Eleventh Revision*) criteria. All training, supervision, and reliability procedures will be overseen by a senior researcher and clinical expert in autism.

#### Plans to Promote Participant Retention and Complete Follow-Up

To enhance participant retention and ensure follow-up assessments, several initiatives will be taken. Participants will be contacted by phone approximately 1 week before the planned follow-up assessments, and travel expenses for public transportation will be compensated to reduce the financial burden associated with participation in the trial. Additionally, assessors can rearrange scheduled assessment times to accommodate participants’ needs. In cases where participants leave the trial prematurely, efforts will be made to complete follow-up assessments. If participants are unable to complete the full assessment battery, priority will be given to obtaining the primary and secondary outcomes.

### Data Management

Data from evaluation of eligibility and assessments during the trial will be entered directly into the electronic case report form using the data entry system REDCAP. REDCAP is an electronic data capture tool hosted by the Center for IT, Medical Technology and Telephony (CIMT) in the Capital Region of Denmark. When electronic entry is not possible, data will be collected on paper and later transferred into REDCAP. Data on paper will be stored locally and secured. Using REDCAP, surveys can securely be distributed and returned via E-boks, a public Danish digital mailing system that all citizens possess, reducing the risk of data loss and unauthorized access. Data for each participant will be linked to a unique serial number, with only assigned researchers having access to REDCAP. REDCAP includes a complete audit trail of data transactions, detailed user rights, and access control management, ensuring compliance with Danish legislation (the Act on Processing Personal Data). Research data will be exported from REDCap without personal identifiers. Data will be exported to well-known software packages (eg, SPSS [IBM Corp], SAS [SAS Institute], Stata [StataCorp LLC], and R [R Foundation for Statistical Computing]) and placed in logged folders on a network drive under the control of the CIMT. A data manager will ensure that all variables are properly defined with variable and value labels. All derived variables will be properly defined, and algorithms will be kept in special files. All data will be examined carefully to identify errors in data entry.

### Statistical Analysis of Primary and Secondary Outcomes

Analyses will be performed on the intention-to-treat population for the primary and secondary end points, that is, analyzing all randomized participants according to the arm they were randomized to. The analysis method will be ANCOVA (analysis of covariance) of change from baseline with treatment as a factor and baseline value as a covariate at the corresponding postbaseline visit, that is, third month. Additionally, stratification variables and baseline values of social anxiety, alexithymia, and social function will be included as covariates. Treatment difference point estimates will be reported together with 95% CIs and *P* value. Missing data will be handled using multiple imputation. For the exploratory end points, a modified intention-to-treat set will be used, requiring at least 1 postbaseline measurement for the inclusion in the analysis for each end point. The analysis method will be the linear mixed effects model. Results will be reported for both postbaseline visits. Details of model specifications, imputation methods and assumptions, sensitivity analyses, and subgroup analyses will be provided in the forthcoming statistical analysis plan, if applicable. Results will be reported with a 95% CI and *P* value, using a 5% significance level. Baseline demographic and clinical characteristics will be summarized for each group, using descriptive statistics (eg, means, SDs, medians, and ranges for continuous variables and frequencies and proportions for categorical) to assess comparability between groups at baseline. Efficacy analysis will be conducted by a blinded and independent statistician with no contact with the participants in the trial. Reporting will follow CONSORT (Consolidated Standards of Reporting Trials) guidelines [85].

To address potential confounding from changes in psychotropic medication, we will conduct sensitivity analyses to explore whether medication changes influence the primary and secondary outcomes. Medication type and dosage are documented at both follow-up time points (3 and 6 months post baseline). To account for variability in TAU, we document the type, frequency, and duration of TAU received during two predefined periods (1) from enrollment to the 3-month follow-up and (2) from 3- to 6-month follow-up. If systematic between-group differences in TAU exposure emerge, summary TAU variables (eg, number of sessions and service type) will be included as covariates in a sensitivity analysis to adjust for potential confounding. Additionally, exploratory analyses may be conducted to examine whether specific aspects of TAU moderate the intervention effect. In addition, exploratory subgroup analyses will be conducted to examine whether selected baseline characteristics moderate the effect of the intervention on primary and secondary outcomes. Analyses will be based on several prespecified variables, including sex, alexithymia, social anxiety, depression, and ADHD.

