#### Relevant Concomitant Care and Interventions Permitted or Prohibited During the Trial

The prevalence of co-occurring psychiatric diagnoses is considered high among autistic adults, with ADHD (25.7%) being the most prevalent comorbid condition, followed by mood disorders (18.8%) and anxiety disorders (17.8%) [50]. The estimated prevalence of ADHD in the total autistic population is varying widely in the literature. Recent meta-analyses estimate the pooled point prevalence rate of ADHD in the autistic population to range from 28% to approximately 38% [51,52]. To enhance the ecological validity of the trial, co-occurring psychiatric conditions and associated medical treatments will not constitute exclusion criteria apart from medically untreated ADHD. As previously mentioned, participants with co-occurring ADHD must demonstrate a preliminary satisfactory treatment response to ADHD medication at the time of enrollment. This determination will be based on mutual agreement between the participant and the clinician responsible for their ADHD treatment, confirming that targeted ADHD symptoms are well managed. Additionally, no changes in the type or dosage of ADHD medication are permitted within the 4 weeks preceding enrollment in the trial. This criterion is essential due to the relatively high prevalence of co-occurring ADHD in individuals on the autism spectrum. Further, many adults are often being assessed for (and diagnosed with) ADHD while undergoing evaluation for autism. As a result, many potential participants may be titrating ADHD medication while being referred to the trial. To be able to effectively distinguish the effects of the trial intervention from those of ADHD medication, this criterion is essential. Furthermore, all psychopharmacological treatments will be thoroughly mapped and documented upon trial completion.

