### Allocation

#### Sequence Generation

Participants who provide signed informed consent and meet the eligibility criteria will be randomly allocated to receive either TAU or VRSCT+TAU upon completion of the baseline assessment. Randomization will be performed using a centralized, automated, computer-generated randomization module in the online REDCAP (Research Electronic Data Capture; Vanderbilt University) system (refer to “Data Management” section). A stratified block randomization with a concealed randomization sequence will be used, with block sizes that are variable and unknown to the investigators. Randomization will be stratified by site and sex. The allocation of the randomized intervention will remain concealed to investigators and assessors until the statistical analyses of outcome data have been completed.

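### The planned sensitivity analysis adjusts for TAU received after randomisation and calls it a correction for confounding; a systematic arm difference in TAU follows from allocation, so the adjusted estimate can be biased and has no stated target

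*Protocol article*

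**What the plan says.** All places are in the protocol article.

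- **TAU rule** (Statistical Analysis of Primary and Secondary Outcomes): "If systematic between-group differences in TAU exposure emerge, summary TAU variables (eg, number of sessions and service type) will be included as covariates", and this is done "in a sensitivity analysis to adjust for potential confounding".
- **When TAU is recorded** (same section): in two windows, "1) from enrollment to the 3-month follow-up and (2) from 3- to 6-month follow-up".
- **When randomisation happens** (Sequence Generation): participants "will be randomly allocated to receive either TAU or VRSCT+TAU upon completion of the baseline assessment".
- **Medication** (Statistical Analysis): "To address potential confounding from changes in psychotropic medication, we will conduct sensitivity analyses to explore whether medication changes influence the primary and secondary outcomes". No method is given.
- **Primary analysis** (Statistical Analysis): intention to treat, ANCOVA of change at 3 months. The only covariates are the baseline value, the stratification variables and baseline social anxiety, alexithymia and social function.
- **Blinding** (Blinding): participants, therapists and the clinicians who manage TAU all know the allocation.
- **TAU content** (Explanation for the Choice of Comparator; Limitations): not strictly defined, and expected to vary between participants.

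**The concern.** A confounder of a treatment comparison is a common cause of treatment and outcome. In this trial a random sequence decides treatment, so nothing that happens afterwards can confound the intention-to-treat contrast. TAU sessions used between allocation and 3 months come later, and allocation can change them in an unblinded trial. For example, VRSCT may replace some counselling, or participants allocated to TAU alone may seek more help.

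The trigger makes this worse. The covariates enter when the arm difference is systematic, which is the case where conditioning on TAU can do damage. A chance difference would be harmless.

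Two things can go wrong. If TAU affects SRS-2A, adjustment takes out the part of the effect that runs through TAU, and the result is no longer the total effect. If unmeasured need drives both TAU use and SRS-2A, adjustment links allocation to need within levels of TAU and creates an association that randomisation had excluded. The article names no other target for the adjusted figure, such as a controlled direct effect. A reader would take it as a check on the main result, and a sound result could look fragile, or a null one could look like an effect.

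**Working it through.** **1. The plan's own figure, for scale.** Inputs from Sample Size and Power Calculation: d = 0.5, 80% power, two-sided 5%. n = 2 × (1.960 + 0.842)² / 0.5² = 62.8, so 63 per group. With 10% dropout, 126 / 0.9 = 140. Both figures reproduce. With 63 per arm and unit SD, the standard error of a difference is √(2/63) = 0.178 SD.

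**2. Bias through unmeasured need (all inputs assumed).** Let A be the arm, U unmeasured need, T the TAU received and Y the SRS-2A outcome, with within-arm variances of 1. Lower Y is better.

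- T = −a·A + b·U + error, so the VRSCT arm uses a SD less TAU.
- Y = δ·A + c·U + error, so TAU itself has no effect.
- The within-arm slope of Y on T is b·c. The arms differ in T by −a. The adjusted arm coefficient is therefore δ − (b·c)(−a) = δ + a·b·c.

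Error rate of a nominal 5% test when δ = 0: Φ(−1.96 + B/0.178) + Φ(−1.96 − B/0.178), where B = a·b·c.

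| a | b = c | B (SD) | δ = −0.50 becomes | Error rate if δ = 0 |
|---|---|---|---|---|
| 0.3 | 0.3 | 0.027 | −0.473 | 5.3% |
| 0.3 | 0.5 | 0.075 | −0.425 | 7.1% |
| 0.5 | 0.3 | 0.045 | −0.455 | 5.7% |
| 0.5 | 0.5 | 0.125 | −0.375 | 10.8% |
| 0.8 | 0.3 | 0.072 | −0.428 | 6.9% |
| 0.8 | 0.5 | 0.200 | −0.300 | 20.2% |

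In the last row, using the adjusted model's own standard error, 0.178 × √[(1 − 0.5⁴)(1 + 0.8²/4)] = 0.186, gives 19%.

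**3. Simulation at the planned size.** 63 per arm, 4,000 replicates per scenario, benefit coded positive, and the true total effect set to 0.50 or 0. Inputs are again assumptions.

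| Scenario | Without TAU | With TAU |
|---|---|---|
| VRSCT arm uses 0.5 SD less TAU; TAU has no effect; needier participants use more (loadings 0.4 and −0.5) | 0.50, power 0.80 | 0.40, power 0.60 |
| Same, true effect 0 | 0.00, error 5.0% | −0.10, error 8.8% |
| Same, true effect 0, arm difference reversed | 0.00, error 4.5% | +0.10, error 8.0% |
| TAU a pure mediator (effect 0.3), 0.5 SD less in VRSCT arm | 0.50 | 0.65 |
| TAU a pure mediator, 0.5 SD more in VRSCT arm | 0.50 | 0.35 |
| Mediator plus unmeasured need, 0.5 SD less in VRSCT arm | 0.50 | 0.55 |
| Smaller imbalance (0.2 SD; loadings 0.3 and −0.4) | 0.50 | 0.475 |
| Chance imbalance only | 0.50 | 0.50 |
| Systematic imbalance, TAU unrelated to outcome | 0.50 | 0.50 |

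In the pure-mediator rows the adjusted figure equals the direct effect, 0.50 ∓ 0.5 × 0.3. In the row with mediator and unmeasured need, the total effect is 0.50 and the direct effect 0.65, so 0.55 estimates neither. Leaving TAU out recovers the total effect in every row.

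**The case against.** **Bias is not certain.** This stands. The last two rows of the simulation show none, and a small imbalance gives little. The error rate near 20% needs both a 0.8 SD gap in TAU and loadings of 0.5. The calculation also omits the planned baseline covariates, so U must be the need that remains after them, and 0.5 is generous.

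**An analysis holding TAU fixed can be a fair question when TAU is not standardised.** Also true, but it is a different question from confounding. It needs a named target and the assumption of no unmeasured common cause of TAU and outcome, and the stated rationale gives neither.

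**Details are deferred to the statistical analysis plan.** The section defers model specifications and sensitivity details. However, it already fixes the trigger, the covariates and the rationale, so this is a stated rule and not an omission.

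**The first TAU window starts at enrolment.** A short part of it therefore precedes randomisation. The rest of that window and all of the second follow it, so the argument is unchanged.

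**Stronger readings that the document does not support:**

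- *Medication change is also to be a covariate.* The section uses the word confounding but says only that the influence of changes will be explored. No adjustment is stated.
- *A change in medication from baseline to 3 months cannot be derived.* The article says "Medication type and dosage are documented at both follow-up time points (3 and 6 months post baseline" and elsewhere that "all psychopharmacological treatments will be thoroughly mapped and documented upon trial completion". Neither sentence excludes a baseline record, and silence in a condensed article does not show that none exists.
- *The capture times contradict each other.* Recording TAU by period and mapping it on trial completion are compatible.

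**Conclusion.** The point holds for the TAU-covariate rule. As written, the rule treats a consequence of allocation as a confounder, and it applies when conditioning on TAU can mislead. The resulting estimate can be biased for the intention-to-treat effect in either direction. Through unmeasured need alone the shift is about 0.03 to 0.20 SD under the assumed inputs, with a nominal 5% test running at about 5% to 20%. If TAU is a pure mediator with the assumed effect, the shift is 0.15 SD either way. These sizes rest on assumptions; the article gives no figure for TAU use or its relation to SRS-2A.

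Only a conditional sensitivity analysis is affected. The primary ANCOVA, the sample size and the main test do not depend on it. A reader might infer that the trial's main conclusion is at risk, and it is not. For medication, the criticism is limited to the label.

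**What to change.** 1. Remove the TAU-covariate analysis as a correction for confounding.
2. State that the primary estimate is the effect of offering VRSCT on top of whatever care followed (a treatment-policy strategy). The existing intention-to-treat ANCOVA already fits this.
3. Tabulate TAU type, frequency and duration by arm for each of the two periods already defined.
4. If an adjusted analysis is kept, name its target (for example a controlled direct effect), state that it assumes no unmeasured common cause of TAU and outcome, use a causal method suited to that target, and do not present it as a check on the intention-to-treat result. TAU measured before randomisation may be used as an ordinary baseline covariate.
5. For medication, drop the word confounding and describe changes by arm as post-randomisation events. No adjustment is stated there, so none needs replacing.

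The cost is a few sentences in the protocol and the forthcoming statistical analysis plan, plus one descriptive table from data already planned. No new data collection is needed. It should be settled before the analysis starts, which the article expects in October 2026.

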### Data Monitoring and Oversight

#### Trial Oversight and Management

The trial will be overseen by a Project Management Group (PMG). The PMG will comprise the principal investigator of the study, who is also the trial manager and daily leader of the trial, the principal therapist of the trial, and the supervisor of the assessors. The PMG will hold monthly meetings throughout the recruitment period. There will be no data monitoring committee. The PMG will oversee trial safety and the status of recruitment and retention.

#### Adverse Events

Although VR interventions are generally well tolerated with minimal to no severe side effects or adverse events [28], including among autistic adults [25], some individuals may still experience cybersickness, which is not considered to be serious. Therefore, we do not expect to encounter any serious side effects or adverse events. Side effects and adverse events will be monitored and recorded throughout the study, as well as any complaints about the intervention. The following are considered as adverse events: (1) hospital admissions, (2) suicide attempts, (3) any violent incident necessitating police involvement (whether survivor or accused), (4) self-harming behavior, and (5) all deaths. Any adverse events will be reported to the Committee on Health Research Ethics of the Capital Region Denmark.

#### Auditing Trial Conduct

The leading members of the PMG will continuously ensure that the trial is conducted according to protocol, that data is collected accurately and reliably, and that the safety and rights of the participants are protected. Any necessary revisions to the processes will be discussed at the monthly PMG meetings.

### Ethical Considerations

#### Research Ethics Approval

The study was approved by the Committee on Health Research Ethics in the Capital Region of Denmark (Project ID H-23055504) and by the Danish Data Protection Agency at the Capital Region of Denmark (project ID p-2023‐14488).

#### Protocol Amendments

Protocol amendments must be approved by the Committee on Health Research Ethics of the Capital Region Denmark. Any modifications to the protocol will be documented in the trial registration record (NCT06438536).

#### Consent

Trained psychologists from the VIRTU Research Group will obtain signed informed consent for participation in the STEPS trial. Referred participants will initially receive information about the trial written in layman’s terms, covering the trial’s background, objectives, design, intervention, randomization process, risks, confidentiality, and legal rights. Next, an appointment will be arranged with a trial researcher to ensure participants understand the information provided and accept random assignment to either VRCST+TAU or to TAU alone. If they decide to proceed, they will sign a consent form confirming they have received adequate written and verbal information about the trial’s purpose, method, benefits, and risks, and agree to participate. Written, informed consent to participate will be obtained from all participants, and participants have the right to withdraw from the study at any time and for any reason. Written information about the trial aimed at the participants and the informed consent form is available from the corresponding author.

#### Privacy and Confidentiality

This protocol does not include any personal data or identifying images of participants, nor will such data be included in any subsequent publications reporting the trial results. All data presented in future papers will be fully anonymized to ensure participant confidentiality.

